### Data quality management and data protection

The student interviewers have been thoroughly trained and are being supervised by the study center’s staff. If the interviewers have questions, they can contact the study center’s staff for the duration of the study period. The therapists of both IGs constantly remain in close contact with the study center and discuss all uncertainties and therapeutic progress in regular appointments and intervisions among their colleagues in MMT or BPT from the study headquarter. Regular attendance at therapies and potential adverse events are documented on a weekly basis during the intervention periods. Adverse events are classified by severity into mild, moderate, and severe adverse events. Severe adverse events (SAEs) include, for example, severe head injury, spinal cord injury, mental health crisis resulting in hospitalization, suicide attempt, and death.

To test for interrater reliability, 10% of both the pre- (t0) and post- (t1) MADRS surveys as well as 10% of the qualitative interviews will be rated by two differently paired raters. The quality of the data will be guaranteed by strict data monitoring at the study center over the entire study period.

Data handling is in line with European and German data protection laws, and the information sheet contains a data protection declaration. All sensitive data gathered during the video interviews and physical examinations is being pseudonymized and stored in password-protected devices and programs. The participants’ names, contact information, and corresponding codes are being collected in a separate password-protected document. Only members of the study team have access to this list. Patient information sheets are being digitalized and stored in password-protected devices. Published material will not contain any patient-identifying information. The blood samples taken during the physical examination are either being used up or the residues will be destroyed after the analyses are completed.

### Data analysis

The *IBM SPSS Statistics V.28* software will be used to analyze the data. All relevant primary and secondary outcome variables as well as sociodemographic data will be reported descriptively. Participants who drop out over the course of the study but are still available for the video interviews will still be interviewed. After a missing data evaluation is carried out, missing outcome data will be imputed by EM-Imputation [89]. The primary data analytic strategy will be intention to treat (ITT). As a sensitivity analysis additionally, a per-protocol (PP) analysis will be performed. The significance level will be set at *α* = .05.

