#### Quantitative measurements

The primary hypothesis will be tested via mixed model ANOVAs with which potential interactions between time and group can be detected. To test the first and second hypotheses, a mixed model ANOVA with the between-subjects factor group and the within-subjects factor time as well as the group × time interaction will be calculated. Additionally, multiple regression analyses will be calculated to control for the effects of possible confounding variables (e.g., demographics, additional therapeutic treatments, such as antidepressant medication and psychotherapy).

Secondary outcome variables will be tested in an exploratory fashion with mixed model ANOVAs.

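### Filling in missing MADRS scores once by EM and then running an ANOVA gives standard errors that are too small, or a diluted effect if arm is left out of the EM step

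*Protocol article*

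**What the plan says.** Three statements in the protocol article, under Data analysis and its subsection Quantitative measurements, fix the procedure.

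- Missing data: after an evaluation of missingness, "missing outcome data will be imputed by EM-Imputation [89".
- Primary test: "a mixed model ANOVA with the between-subjects factor group and the within-subjects factor time as well as the group × time interaction will be calculated".
- Analysis sets: "The primary data analytic strategy will be intention to treat (ITT). As a sensitivity analysis additionally, a per-protocol (PP) analysis will be performed".

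SPSS V.28 is the named software and alpha is .05. The article does not mention more than one completed data set, a pooling rule, or a correction of the standard error. It does not list the variables that enter the EM step. It gives no expected dropout rate. The MADRS is assessed before treatment (t0), after the 10-week intervention (t1) and 12 months after it ends (t2).

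**The concern.** An EM fill replaces a missing score by its best prediction. The ANOVA that follows cannot tell predictions from measurements. It counts the full 40 patients per arm, keeps the full error degrees of freedom, and computes residual variance from data in which the filled-in scores have no scatter around their prediction. The uncertainty of the imputation never reaches the standard error.

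Whether arm is a predictor in the EM step decides which error results:

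- **Arm included:** the group difference is unbiased, but the test is too liberal.
- **Arm left out:** patients with missing scores are moved to the regression line common to all three groups, and the treatment difference shrinks.

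The affected results are the primary ITT tests of both hypotheses (BPT versus CG, MMT versus CG), with an error that grows with dropout in a trial that follows patients to 12 months. The one named sensitivity analysis, per protocol, changes who is analysed and is not designed to test the imputation.

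**Working it through.** **The plan's own figure.** The Sample size estimation section gives 114 for three groups, two measurements, f = 0.295, 80% power and alpha .05. With λ = f²·N·(2−1) and degrees of freedom 2 and N−3, λ = 0.295² × 114 = 9.92 and power is 0.801, so 114 is reproduced. At the planned 120, λ = 10.44 and power is 0.823. This is the group × time F test on t0–t1 change, which the check below uses.

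**Inputs.** From the protocol: n = 40 per arm, ρ = .50, alpha .05, prior effects d = 0.55 to 0.77 (midpoint 0.66). Assumed: MADRS SD 1 at both times, a proportion q of t1 scores missing completely at random, and q = 10, 20 or 30%.

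**Arm in the EM step, by formula.** The change t1 − t0 has variance 2(1−ρ) = 1. It splits into a part predictable from baseline, (1−ρ)² = 0.25, and a residual part, 1−ρ² = 0.75. For a contrast of two arms:

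- true variance = 2·[0.75/(40(1−q)) + 0.25/40]
- variance that the ANOVA reports ≈ (2/40)·[0.75(1−q) + 0.25]

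For q = 20%, the true variance is 2·(0.0234 + 0.00625) = 0.0594 (SE 0.244), and the reported variance is 0.05 × 0.85 = 0.0425 (SE 0.206). The ratio of SEs is 0.85. A nominal 5% test then has error of about 2Φ(−1.96 × 0.846) = 9.7%.

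| Missing | True SE | Reported SE | Ratio | Approx. type I error |
|---|---|---|---|---|
| 10% | 0.233 | 0.215 | 0.92 | 7.0% |
| 20% | 0.244 | 0.206 | 0.85 | 9.7% |
| 30% | 0.257 | 0.197 | 0.77 | 13.3% |

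The reported SE falls as more data are lost, while the true SE rises.

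**Arm in the EM step, by simulation** (3000 runs per setting):

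| Missing | SE ratio | Type I error, BPT–CG contrast | Type I error, group × time F test |
|---|---|---|---|
| 10% | 0.92 | 7.3% | 8.0% |
| 20% | 0.85 | 9.8% | 11.3% |
| 30% | 0.76 | 13.7% | 16.1% |

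Other runs of the same basic design gave 6.5–7.5%, 7.9–10.4% and 13.5–13.9% for the contrast. With three time points and the missing scores at t2, the F test gave 7.4/11.3/16.6%.

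**Arm left out.** A share q of each arm is set to the common regression line, so the expected effect is about d(1−q). For d = 0.66 this is 0.59/0.53/0.46. Simulation gave 0.60/0.53/0.46, with type I error of the F test at 5.5/5.3/5.5%.

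**Remedy checked.** Multiple imputation with arm and baseline in the model, 20 data sets and Rubin's rules (2000 runs):

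| Missing | Type I error | Mean SE vs true SE | Power at d = 0.66 | Power, single fill with arm | Power, single fill without arm |
|---|---|---|---|---|---|
| 10% | 4.5% | 0.234 vs 0.230 | 80% | 86% | 79% |
| 20% | 4.2% | 0.246 vs 0.238 | 74% | 85% | 71% |
| 30% | 4.7% | 0.262 vs 0.260 | 69% | 84% | 62% |

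The multiply imputed effect is about −0.66, so it is unbiased. With arm in the EM step, the power advantage of the single fill is bought with the inflated error rate.

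**The case against.** The strongest reply is about size. No dropout rate is given, and some design features may keep missing MADRS scores rare. Patients who leave treatment are still interviewed if reachable, interviews are by video, and the control group receives vouchers or passes after t1 and t2. At 2.5% missing the simulated error is only 5.6%, and at 5% about 6.4%. This stands and bounds the claim. However, the plan itself expects missing outcomes, and a visit 12 months after treatment may well have more of them.

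Other points:

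- **The two harms are alternatives.** Correct. If arm is omitted there is no false-positive problem, only dilution and lost power. The EM variable list may reasonably be left to a fuller document. But neither choice gives a valid primary analysis.
- **A richer EM model would do better.** One further predictor with an assumed partial correlation of .6 lowered the error to 6.1/8.1/10.3%. It shrinks the inflation but does not remove it, and helps only if the other data are present when the MADRS is missing.
- **The EM step might add random residuals.** A single fill with added noise still gave 7.0/9.1/12.0%.
- **The article does not say single imputation.** True, but an EM fill with no pooling step is naturally read as one completed data set.
- **The model might be a likelihood-based mixed model.** The between/within-subjects wording and the nonsphericity correction point to a repeated-measures ANOVA. In a likelihood model, too, filled-in values would count as observed.
- **The per-protocol set might be completers only.** It would then contain no imputed values and offer a partial check, in a selected group. The article does not define the set.

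**Conclusion.** The concern holds: this is a stated method that gives wrong results when followed, not a detail left open. With arm in the EM step and 20% missing, the nominal 5% error becomes about 10% for an arm-versus-control contrast and about 11% for the group × time test. With arm left out, about a fifth of the effect is lost. The sizes rest on an assumed missing rate of 10–30%, on values missing completely at random, and on a sparse EM model. They fall to about 6% error, or about 5% dilution, at 5% missing, and to nothing with complete data. Dropout related to unobserved outcome was not simulated. The sample size of 114 is not affected by this point.

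**What to change.** Replace the EM sentence with wording such as: *The primary ITT analysis is a likelihood-based linear mixed model for repeated measures on all observed MADRS scores (REML, unstructured covariance), without imputing the outcome. Where imputation is needed (regressions, secondary outcomes), multiple imputation including arm is used, with at least 50 data sets combined by Rubin's rules.* Drop the single EM fill.

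If the team prefers to keep the planned ANOVA, multiple imputation with arm and baseline, pooled by Rubin's rules, is also sufficient; 20 data sets restored the error rate in the check above. The covariance structure and the number of data sets are recommendations, not the only valid choices. A sensitivity analysis for data missing not at random would address the missing-data assumption directly, which the per-protocol analysis does not.

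The change is to analysis wording only. Both methods are standard procedures, and sample size, data collection and patient contact are untouched. The cost is wider confidence intervals and lower, but honest, power.

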#### Quantitative measurements

The primary hypothesis will be tested via mixed model ANOVAs with which potential interactions between time and group can be detected. To test the first and second hypotheses, a mixed model ANOVA with the between-subjects factor group and the within-subjects factor time as well as the group × time interaction will be calculated. Additionally, multiple regression analyses will be calculated to control for the effects of possible confounding variables (e.g., demographics, additional therapeutic treatments, such as antidepressant medication and psychotherapy).

Secondary outcome variables will be tested in an exploratory fashion with mixed model ANOVAs.

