**Methods:**

The study is being conducted as a randomized controlled intervention trial. Adult participants with unipolar depression are being randomized into three groups (BPT, MMT, or CG), and the first two groups are undergoing a 10-week treatment phase. CG follows their individual standard treatment as usual. A priori power analysis revealed that about 120 people should be included to capture a moderate effect. The primary outcome of the study is depression rated with the Montgomery and Asberg Depression Rating Scale (MADRS) before (t0), directly after (t1), and 12 months after the intervention phase (t2). Data are being collected via questionnaires, computer-assisted video interviews, and physical examinations. The primary hypotheses will be statistically analyzed by mixed model ANOVAs to compare the three groups over time. For secondary outcomes, further multivariate methods (e.g., mixed model ANOVAs and regression analyses) will be conducted. Qualitative data will be evaluated on the basis of the qualitative thematic analysis.

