#### Research hypothesis

I.Patients in the bouldering psychotherapy (BPT) improve significantly more than patients in the control group (CG) regarding the severity of depression.II.Patients in the mental model therapy (MMT) improve significantly more than patients in the control group (CG) regarding the severity of depression.

Effects on secondary outcomes (e.g., anxiety, self-efficacy) will be analyzed in an exploratory fashion. Regarding the biomarkers, it is expected that participation in the BPT will lead to a greater increase in blood osteocalcin and brain-derived neurotrophic factor levels than in the MMT and CG. We expect higher serum acid sphingomyelinase activities to correlate with greater improvement in depression severity in both treatment groups. Additional sphingolipid parameters, growth factors, and inflammatory markers will be analyzed and are expected to normalize in both IGs. Whereas these assumptions were based on previous studies, sample size estimation was based solely on the number of participants required for the psychotherapeutic effect and not adjusted any further.

Qualitative data will be used to explore the extent to which participants perceive the interventions to be helpful, which components or factors of influence they feel are most important, and which limitations or barriers they perceive. In line with Grawe [50], the results of the qualitative analysis will be used to further develop hypotheses on potential factors of influence with respect to BPT and MMT.

In this article, we describe the study protocol for *new ways to cope with depression*. This protocol will serve as a reference for the forthcoming papers that will report the results of the study.

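### Hypotheses I (BPT vs CG) and II (MMT vs CG) are both assigned to one three-group group × time interaction, which identifies neither comparison

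*Protocol article*

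**What the plan says.** Under Research hypothesis there are two confirmatory statements, each comparing one therapy with the control group and each with a direction. Hypothesis I: "Patients in the bouldering psychotherapy (BPT) improve significantly more than patients in the control group (CG) regarding the severity of depression". Hypothesis II: "Patients in the mental model therapy (MMT) improve significantly more than patients in the control group (CG) regarding the severity of depression".

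Under Quantitative measurements, one model is assigned to both: "To test the first and second hypotheses, a mixed model ANOVA with the between-subjects factor group and the within-subjects factor time", with the group × time interaction. The abstract describes the same thing: "The primary hypotheses will be statistically analyzed by mixed model ANOVAs to compare the three groups over time". Under Data analysis one level is given: "The significance level will be set at *α* = .05".

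Sample size estimation powers the interaction of three groups by two repeated measures (f = 0.295, power 80%, α = .05, correlation .50), giving 114, rounded up to 120 or 40 per group. The primary outcome itself is measured three times: "before (t0), directly after (t1), and 12 months after the intervention phase (t2").

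The article names no BPT–CG or MMT–CG contrast, and does not say which of t1 and t2 decides the hypotheses.

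**The concern.** A significant three-group interaction means only that the groups do not all change alike. It can arise because one therapy beats CG, because both do, because the two therapies differ from each other, or because a therapy does worse than CG. It therefore does not answer I or II, yet it is the test the article names for both and the only effect for which the sample size was computed.

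At stake is what the trial may claim for each therapy. This matters most for MMT: by the protocol's own account it goes straight into a randomized trial without a previous open trial, so this is its first test. The article also says that it will serve as the reference for the results papers, so readers will hold the results to the test named here.

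**Working it through.** **1. The plan's own figure.** Inputs from Sample size estimation: 3 groups, 2 measurements, f = 0.295, α = .05, power 80%. The interaction has (3−1)(2−1) = 2 and (N−3)(2−1) = N−3 degrees of freedom. With noncentrality λ = f²N:
- N = 114: λ = 0.295² × 114 = 9.92; critical F(2, 111) = 3.08; power = 0.801.

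So 114 reproduces exactly for the 2-df interaction. The planned size belongs to that test and to neither pairwise hypothesis.

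**2. What the interaction can tell apart.** Take 40 per arm and d = .59, which is 2 × 0.295 and lies within the .55 to .77 that the plan cites. Express d on the SD of the t0–t1 change; at the plan's correlation of .50 this equals the SD of a single score, because 2σ²(1 − .50) = σ².
- Only BPT works, effects (d, 0, 0): λ = 40 × (2/3) × .59² = 9.28; power on 2 and 117 df = 0.77.
- Only MMT works, (0, d, 0): same λ, 0.77.
- Both work, (d, d, 0): the sum of squares about the mean is again (2/3)d², so 0.77.

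The three situations are indistinguishable by this test. Simulation (3 × 40, 117 df) agrees at 77%.

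**3. Family-wise error of two contrasts against CG.** BPT–CG and MMT–CG share the control arm, so with equal arms their correlation is 0.5.
- Each at two-sided .05, run whatever the interaction shows: 1 − P(|Z₁| < 1.96, |Z₂| < 1.96) = 0.0907 (independent tests would give 1 − .95² = 0.0975). Counting only false claims of benefit: about 0.045.
- Run only after a significant three-group, two-time interaction: about 4% under the global null (4.1% to 4.2% across simulations), and 5.0% when one therapy works. If all three arms are equal, the interaction is itself a .05 test; if one therapy works, only one true null is left.
- Bonferroni, .025 each: 0.0465. Dunnett: about .027 each gives .05.

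**4. If t2 enters the interaction** (three times, 4 df). Under the global null the gate still holds: 0.027 for the two t1 contrasts. If effects exist only at t2, the interaction is significant for that reason, and the two t1 contrasts have family-wise error 0.090. If only BPT works and MMT is tested at both t1 and t2, the error for MMT is also 0.090.

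**5. Power per contrast, 40 per arm, two-sided .05, d = .59.**

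| Situation | Power for the contrast |
|---|---|
| No gate | 74% |
| Gate; other therapy has no effect, or the same effect | 69% |
| Gate; other therapy has half the effect (.295) | 63% |

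At the ends of the cited range, without a gate, the normal approximation gives 69% (d = .55) and 93% (d = .77).

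**The case against.** The strongest reply is that the article never says a significant interaction confirms both hypotheses. It says a mixed ANOVA will be calculated, and follow-up contrasts and their adjustment are commonly left to a fuller document not shown here. In ordinary use such contrasts follow a significant omnibus test, and for the three-group, two-time model that was powered, that practice already controls family-wise error. This stands, and it rules out three stronger readings:

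- A reader might infer that the plan runs at about 9% family-wise error. That figure belongs to contrasts run without the interaction as a gate, which the document does not say will be done. It also counts errors in both directions.
- A reader might infer that MMT will be declared effective in 77% of trials in which only BPT works. That assumes nobody looks at the MMT–CG difference, and the document states no such rule. The 77% shows only that the named test does not speak to MMT.
- A reader might infer that success could often be claimed when neither therapy differs from CG. In that case the interaction is significant only 5% of the time. Higher figures need a scenario such as BPT 0.3 SD better and MMT 0.3 SD worse than CG: significant in 66% of trials, and in 18% with neither contrast significant. There both therapies truly differ from CG, and nothing in the protocol anticipates a harmful therapy.

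What the reply does not remove is that the article itself names the test for I and II. An analysis plan using the two contrasts would be replacing a stated test, not filling in a detail.

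**Conclusion.** The point holds as a mismatch between hypotheses and test. Two directional comparisons with CG are assigned to one non-directional 2-df interaction, and the sample size of 114 reproduces for that interaction only. At d = .59 with 40 per arm it is significant in about 77% of trials whichever of the therapies works, so it cannot support I or II on its own. An uncontrolled error rate is not established; whether there is one depends on how the contrasts are run and on whether t2 is in the interaction, neither of which the article settles.

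The figures assume normal data, equal variances, equal arms of 40, d on the SD of the t0–t1 change, and no dropout, since the article gives no dropout rate.

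**What to change.** State under Quantitative measurements that hypotheses I and II are tested by the BPT–CG and MMT–CG contrasts in MADRS change from t0 to t1, each declared significant at two-sided .05 only if the three-group, two-time (t0, t1) group × time interaction is also significant at .05. Report both differences with 95% confidence intervals, treat BPT–MMT as exploratory, and report t2 as follow-up.

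Say openly that t1 is a choice. It matches the two-measurement model used for the sample size, but the article lists t0, t1 and t2 for the primary outcome without ranking them. If t2 is kept in the interaction, the gate no longer protects fully, and the two contrasts at the deciding time point need Bonferroni (.025 each) or Dunnett (about .027 each). Making both t1 and t2 confirmatory would mean four contrasts, which these two-contrast levels do not cover.

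The change takes a few sentences, needs no new data and keeps the planned ANOVA. Its price is power: at d = .59, about 74% per contrast falls to 69%, or to 63% if the other therapy has half the effect, before any dropout. The planned 80% should be described as the power of the interaction, with power per contrast given beside it.

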### Study design and setting

The study was designed as a randomized, controlled, interventional, prospective, longitudinal, assessor-blinded study with three arms (BPT, MMT, CG). The overall start date was on October 1, 2021. Recruitment began on March 29, 2022, and will continue through February 28, 2023, in the Erlangen/Nuremberg/Fuerth region, a metropolitan region of three cities. After passing a diagnostic screening interview, participants are randomly assigned to one of the IGs (BPT or MMT) or the CG. Both IGs consist of 10 weekly 2-h sessions with a maximum of 11 participants and are each led by two therapists. After the end of the intervention phase, participants in the CG will be offered preferential admission to an outpatient BPT group at University Hospital Erlangen. MMT will be directly evaluated in an RCT design because many of its single components are well-established and well-investigated cognitive distortions. As it is very unlikely that the novel long-term focus on transforming thinking errors into appropriate goal-oriented thinking and action could lead to significant side effects, a previous open trial was not deemed mandatory. In all four consecutive waves of the study, the interventions are taking place simultaneously. To collect the data, structured video interviews are being conducted at baseline before the onset of therapy (t0), after the intervention (t1), and 12 months after the end of the intervention (t2). In addition to the interviews, participants are required to complete a series of questionnaires online (at t0, t1, and t2) and to undergo a physical examination with blood sampling (at t0 and t1 at about the same time of day). All procedures were approved by the Friedrich-Alexander-Universität Erlangen-Nürnberg Ethics Committee (Ref. 21-332-B) on December 13, 2021. The SPIRIT participant timeline is shown in Fig. 1, and the SPIRIT checklist is provided as an Additional file [51]. Trial Registration Data are presented in Table 1 (ISRCTN12347878, Registration date: March 28, 2022, registered prospectively).

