### Sample size estimation

ITT sample size was calculated on the basis of the authors’ previous experiences with BPT. Both studies on the effectiveness of BPT showed a moderate effect size (Cohen’s *d*s of 0.55 to 0.77) on depression severity [24, 25]. On the basis of effect sizes for CBT [9], comparable effect sizes are expected for MMT. Thus, an a priori power analysis to identify a moderate effect of *f* ≥ 0.295 was computed with the statistical program *G*Power* version 3.1.9.7. The calculations for the mixed ANOVA with two repeated measures as within-subjects factors and three groups as between-subjects factors and a group × time interaction revealed a total sample size of 114 participants. Power was set at 80%, *α* = .05, a correlation between repeated measurements of .50, and a nonsphericity correction of 1. To create three equal-sized groups each consisting of 10 participants across the four waves of recruitment, we planned to recruit a total of 120 participants, resulting in a total of 40 participants per group.

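### The primary ANOVA and the sample size treat all patients as independent although BPT and MMT are delivered in four therapy groups of about 10 each; if outcomes correlate within those groups, standard errors against control are too small

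*Protocol article*

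**What the plan says.** **Delivery.** Study design and setting states: "Both IGs consist of 10 weekly 2-h sessions with a maximum of 11 participants and are each led by two therapists". It also says that the interventions run simultaneously in all four waves. The BPT and MMT sections each give a group size of about 10. The Control group section describes treatment as usual with nothing study-specific during the intervention phase, then an offer of preferential admission to the outpatient BPT group after t1.

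**Analysis.** Under Quantitative measurements, both hypotheses are tested by "a mixed model ANOVA with the between-subjects factor group and the within-subjects factor time", together with the interaction of the two factors. As a supplement, "multiple regression analyses will be calculated to control for the effects of possible confounding variables"; the examples given are demographics and concurrent treatment, all of them patient characteristics. Data analysis adds: "The significance level will be set at *α* = .05".

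**Sample size.** The calculation for three groups and two repeated measures gave 114. Its settings were: "Power was set at 80%, *α* = .05, a correlation between repeated measurements of .50, and a nonsphericity correction of 1". That correlation is between measurements on the same person. The rise to 120 is explained by group filling: "To create three equal-sized groups each consisting of 10 participants across the four waves of recruitment". No correlation between members of a therapy group, design effect or therapist term appears anywhere in the article.

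**The concern.** This is a partially nested design. Patients in BPT or MMT share ten sessions, a pair of therapists and the dynamics of one group, whereas controls up to t1 share nothing that the study provides. In the stated ANOVA, group means treatment arm, and mixed means a combination of between- and within-subject factors. The patient is the only source of error, so variation between therapy groups is left out of the standard error.

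Randomization does not remove this variation, because it arises after allocation. Blinded rating does not remove it either. The trial measures group cohesion and interpersonal learning (FEPiG) as possible factors of influence, so its authors consider it plausible that group process matters.

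For any positive ICC, leaving out the therapy-group variance pushes the error rate up. The contrasts affected are the only two primary hypotheses, each intervention against control. The lost information also makes the power lower than the sample size section suggests.

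**Working it through.** **1. The plan's own figure.** Inputs from Sample size estimation: f = .295, three arms, two measurements, alpha .05, power 80%. A noncentral F test with df = 2 and N - 3 and noncentrality f² × N reaches 80.1% power at N = 114 and 82.3% at N = 120. So 114 reproduces, and the calculation assumes independent patients.

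**2. Cluster structure.** Four waves with 10 patients per arm per wave give four therapy groups of 10 in BPT, four in MMT and 40 ungrouped controls (to t1).

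**3. Formulas, on the change score with unit variance.**
- Design effect in an intervention arm: DE = 1 + (10 - 1) × ICC.
- Effective size of 40 patients: 40 / DE.
- True over reported standard error for one intervention arm against control: √((DE + 1) / 2).
- Large-sample error at nominal 5%: 2 × (1 - Φ(1.96 / ratio)).

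Example at ICC .05: DE = 1 + 9 × .05 = 1.45; 40 / 1.45 = 27.6; ratio = √(2.45 / 2) = 1.107; error = 2 × (1 - Φ(1.771)) = 7.7%.

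**4. Results.** The ICC values are assumptions. The simulations used 40,000 trials per setting with the test that ignores clustering. The last two columns add a wave effect shared by all arms, with variance .05 or .10 of the unit variance (also assumed).

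| ICC | DE | Effective n of 40 | SE ratio | Error, formula | Error, simulated, no wave effect | Wave variance .05 | Wave variance .10 |
|---|---|---|---|---|---|---|---|
| 0 | 1.00 | 40.0 | 1.00 | 5.0% | about 5% | 4.8% | 4.3% |
| .01 | 1.09 | 36.7 | 1.02 | 5.5% | about 5.5% | 5.1% | 4.6% |
| .02 | 1.18 | 33.9 | 1.04 | 6.0% | about 6.2% | 5.7% | 5.4% |
| .05 | 1.45 | 27.6 | 1.11 | 7.7% | about 7.5% | 7.2% | 6.7% |
| .10 | 1.90 | 21.1 | 1.20 | 10.4% | about 10.6% | 10.0% | 9.3% |

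Formula and simulation agree to about 0.2 percentage points. The three-arm F test without a wave effect has a larger error (about 10% at ICC .05 and 15.5% at .10), but Hypotheses I and II are single contrasts.

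**5. Power of one contrast.** Reading f = .295 as d / 2 gives d = 2 × .295 = .59, inside the cited range of .55 to .77. With SE = √((DE + 1) / 40):
- ICC 0: SE = √(2 / 40) = .224. Power is 75% by the normal approximation and 74% by the t test.
- ICC .05: SE = √(2.45 / 40) = .247; Φ(.59 / .247 - 1.96) = 66%.
- ICC .10: SE = √(2.90 / 40) = .269; Φ(.59 / .269 - 1.96) = 59%, and 58% by the t test.

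Degrees of freedom that reflect four groups per arm lower this further. A Satterthwaite test comparing therapy-group means with individual controls held its error near 5% and had about 71, 61 and 53% power at ICC 0, .05 and .10. That test has no wave term, so these figures only indicate what the model proposed below would give.

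**The case against.** - **The size rests on an ICC that the documents do not give.** This stands. At .01 the excess is about half a percentage point. Measuring group cohesion makes a zero ICC doubtful but says nothing about its size for blinded MADRS change.
- **A shared wave effect works the other way.** Allocation is balanced within wave, so ignoring wave makes the ANOVA conservative. This stands in part: at ICC .01 it can cancel the inflation, at .05 it leaves about 7%, and at .10 about 9-10%.
- **Controls are ungrouped only to t1.** This stands. Some may later join outpatient BPT, so the partial nesting as described applies to t0-t1 and cannot be carried over to t2.
- **The therapy group is not the only layer.** This stands. Each intervention draws therapist pairs from three people, so pairs across four groups must overlap. BPT also splits into two halves in the action phase, and MMT uses rotating subgroups. An independent effect per group of 10 is an approximation.
- **An article condenses, and an analysis plan may hold the detail.** This does not answer the point. The article states the primary model and a reproducible sample size, and both treat patients as independent. The word mixed does not imply a random therapy-group effect, because the article defines the model by its between- and within-subject factors.

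**Conclusion.** The point holds in conditional form. The stated primary model and sample size ignore the therapy groups in two of the three arms. If the within-group correlation is positive, the standard errors of both primary contrasts are too small. For assumed ICCs of .01 to .10 without a wave effect, the true error of one contrast is about 5.5 to 10.6% instead of 5%, and somewhat less with a common wave effect. Power per contrast at d = .59 and 40 per arm is about 74% at ICC 0, 66% at .05 and 58-59% at .10, before any small-sample correction.

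A reader might infer that the 5% level is certainly breached for both hypotheses. The documents do not support that, since they give no ICC, and a small ICC together with a wave effect could leave the error at or below 5%. A reader might also take the error of about 15% for the three-arm test as the headline. That figure needs an ICC of .10 and no wave effect, and it does not belong to the single-arm contrasts stated as hypotheses. Nor should the whole argument be extended to t2 unchanged.

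**What to change.** 1. Make the primary t0-t1 analysis a partially nested mixed model: a random therapy-group effect (wave × arm) in BPT and MMT only, each control as its own unit, wave as a fixed effect, and Satterthwaite or Kenward-Roger degrees of freedom.
2. Report the estimated ICC. Four groups per arm estimate it poorly, so prespecify a sensitivity analysis over a fixed range, for example 0 to .10.
3. At t2, take account of controls who joined the outpatient BPT group after t1 instead of assuming that each is independent.
4. State in the sample size section that no clustering allowance was made, and give per-contrast power over the same ICC range. Compute it for the model in item 1, including its wave term and degrees of freedom.
5. Name therapist overlap across groups as a limitation that this design cannot separate.

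**Cost.** For t0-t1 the change is wording and analysis code, because wave and arm are already known. Item 3 needs a record of which controls entered outpatient BPT; the interviews at t1 and t2 already ask about changes in psychotherapeutic treatment. The price is wider intervals and lower power. The change should be fixed before outcome data are analysed.
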